## 9.4. Overall survival (OS)

Overall survival (months) is defined as the time from the date of enrolment until death due to any cause. Any patient not known to have died at the time of analysis will be censored based on the last recorded date on which the patient was known to be alive. Overall survival data will be collected at 12 months.

Subjects who have disease control following completion of 12 months of treatment or subjects who are withdrawn from durvalumab + tremelimumab treatment for reasons other than confirmed PD will continue to have objective tumor assessments (see Appendix 3).

## **10. ASSESSMENT OF SAFETY**

The Principal Investigator is responsible for ensuring that all staff involved in the study is familiar with the content of this section.

### **10.1. Safety Parameters**

#### **10.1.1. Definition of adverse events**

The International Conference on Harmonization (ICH) Guideline for Good Clinical Practice (GCP) E6 (R1) defines an AE as:

Any untoward medical occurrence in a patient or clinical investigation subject administered a pharmaceutical product and which does not necessarily have a causal relationship with this treatment. An AE can therefore be any unfavorable and unintended sign (including an abnormal laboratory finding), symptom, or disease temporally associated with the use of a medicinal product, whether or not considered related to the medicinal product.

An AE includes but is not limited to any clinically significant worsening of a subject's pre-existing condition. An abnormal laboratory finding (including ECG finding) that requires an action or intervention by the investigator, or a finding judged by the investigator to represent a change beyond the range of normal physiologic fluctuation, should be reported as an AE.

Adverse events may be treatment emergent (ie, occurring after initial receipt of investigational product) or nontreatment emergent. A nontreatment-emergent AE is any new sign or symptom, disease, or other untoward medical event that begins after written informed consent has been obtained but before the subject has received investigational product.

Elective treatment or surgery or preplanned treatment or surgery (that was scheduled prior to the subject being enrolled into the study) for a documented pre-existing condition, that did not worsen from baseline, is not considered an AE (serious or nonserious). An untoward medical event occurring during the prescheduled elective procedure or routinely scheduled treatment should be recorded as an AE or SAE.

The term AE is used to include both serious and non-serious AEs.

#### **10.1.2. Definition of serious adverse events**

A serious adverse event is an AE occurring during any study phase (i.e., screening, run-in, treatment, wash-out, follow-up), at any dose of the study drugs that fulfils one or more of the following criteria:

- Results in death
- Is immediately life-threatening

- Requires in-patient hospitalization or prolongation of existing hospitalization
- Results in persistent or significant disability or incapacity
- Is a congenital abnormality or birth defect in offspring of the subject
- Is an important medical event that may jeopardize the patient or may require medical intervention to prevent one of the outcomes listed above:
- Medical or scientific judgment should be exercised in deciding whether expedited reporting is appropriate in this situation. Examples of medically important events are intensive treatment in an emergency room or at home for allergic bronchospasm, blood dyscrasias, or convulsions that do not result in hospitalizations; or development of drug dependency or drug abuse.

The causality of SAEs (their relationship to all study treatment/procedures) will be assessed by the investigator(s) and communicated to AstraZeneca.

#### **10.1.3. Durvalumab + tremelimumab adverse events of special interest**

An adverse event of special interest (AESI) is one of scientific and medical interest specific to understanding of the Investigational Product and may require close monitoring and rapid communication by the investigator to the sponsor. An AESI may be serious or non-serious. The rapid reporting of AESIs allows ongoing surveillance of these events in order to characterize and understand them in association with the use of this investigational product.

AESIs for durvalumab and tremelimumab include but are not limited to events with a potential inflammatory or immune-mediated mechanism and which may require more frequent monitoring and/or interventions such as steroids, immunosuppressants and/or hormone replacement therapy. These AESIs are being closely monitored in clinical studies with durvalumab monotherapy and combination therapy. An immune-related adverse event (irAE) is defined as an adverse event that is associated with drug exposure and is consistent with an immune-mediated mechanism of action and where there is no clear alternate aetiology. Serologic, immunologic, and histologic (biopsy) data, as appropriate, should be used to support an irAE diagnosis. Appropriate efforts should be made to rule out neoplastic, infectious, metabolic, toxin, or other etiologic causes of the irAE.

If the Investigator has any questions in regards to an adverse event (AE) being an irAE, the Investigator should promptly contact the Study Physician.

AESIs observed with durvalumab and tremelimumab include:

- Diarrhea / Colitis and intestinal perforation
- Pneumonitis / ILD
- hepatitis / transaminase increases
- Endocrinopathies (i.e. events of hypophysitis/hypopituitarism, adrenal insufficiency, hyper- and hypothyroidism and type I diabetes mellitus)
- Rash / Dermatitis
- Nephritis / Blood creatinine increases
- Pancreatitis / serum lipase and amylase increases
- Myocarditis

- Myositis / Polymyositis
- Neuropathy / neuromuscular toxicity (e.g. Guillain-Barré, and myasthenia gravis)

Other inflammatory responses that are rare / less frequent with a potential immune-mediated aetiology include, but are not limited to, pericarditis, sarcoidosis, uveitis and other events involving the eye, skin, haematological and rheumatological events, vasculitis, non-infectious meningitis and non-infectious encephalitis.

Further information on these risks (e.g. presenting symptoms) can be found in the current version of the durvalumab and tremelimumab Investigator Brochure. For durvalumab and tremelimumab, AESIs will comprise the following:

### **Pneumonitis**

AEs of pneumonitis are also of interest for AstraZeneca, as pneumonitis has been observed with use of anti-PD-1 mAbs (but not with anti-PD-L1 mAbs). Initial work-up should include a high-resolution CT scan, ruling out infection, and pulse oximetry. Pulmonary consultation is highly recommended. Guidelines for the management of patients with immune-related AEs (irAEs) including pneumonitis are provided in Table 1.

### **Infusion reactions**

AEs of infusion reactions (also termed infusion-related reactions) are of special interest to AstraZeneca and are defined, for the purpose of this protocol, as all AEs occurring from the start of IP infusion up to 48 hours after the infusion start time. For all infusion reactions, SAEs should be reported to AstraZeneca Patient safety as described in Section 10.3.

### **Hypersensitivity reactions**

Hypersensitivity reactions as well as infusion-related reactions have been reported with anti-PD-L1 and anti-PD-1 therapy (Brahmer et al 2012). As with the administration of any foreign protein and/or other biologic agents, reactions following the infusion of mAbs can be caused by various mechanisms, including acute anaphylactic (IgE-mediated) and anaphylactoid reactions against the mAbs and serum sickness. Acute allergic reactions may occur, may be severe, and may result in death. Acute allergic reactions may include hypotension, dyspnea, cyanosis, respiratory failure, urticaria, pruritus, angioedema, hypotonia, arthralgia, bronchospasm, wheeze, cough, dizziness, fatigue, headache, hypertension, myalgia, vomiting, and unresponsiveness. Guidelines for the management of patients with hypersensitivity (including anaphylactic reaction) and infusion-related reactions are provided in Table 1.

### **Hepatic function abnormalities (hepatotoxicity)**

Hepatic function abnormality is defined as any increase in ALT or AST to greater than  $3 \times$  ULN and concurrent increase in total bilirubin to be greater than  $2 \times$  ULN. Concurrent findings are those that derive from a single blood draw or from separate blood draws taken within 8 days of each other. Follow-up investigations and inquiries will be initiated promptly by the investigational site to determine whether the findings are reproducible and/or whether there is objective evidence that clearly supports causation by a disease (eg, cholelithiasis and bile duct obstruction with distended gallbladder) or an agent other than the IP are provided in Table 1.

## **Gastrointestinal disorders**

Diarrhea/colitis is the most commonly observed treatment emergent SAE when tremelimumab is used as monotherapy. In rare cases, colon perforation may occur that requires surgery (colectomy) or can lead to a fatal outcome if not properly managed. Guidelines on management of diarrhea and colitis in patients receiving tremelimumab are provided in Table 1.

## **Endocrine disorders**

Immune-mediated endocrinopathies include hypophysitis, adrenal insufficiency, and hyper- and hypothyroidism. Guidelines for the management of patients with immune-mediated endocrine events are provided in Table 1.

## **Pancreatic disorders**

Immune-mediated pancreatitis includes autoimmune pancreatitis, and lipase and amylase elevation. Guidelines for the management of patients with immune-mediated pancreatic disorders are provided in Table 1.

## **Neurotoxicity**

Immune-mediated nervous system events include encephalitis, peripheral motor and sensory neuropathies, Guillain-Barré, and myasthenia gravis. Guidelines for the management of patients with immune-mediated neurotoxic events are provided in Table 1.

## **Nephritis**

Consult with Nephrologist. Monitor for signs and symptoms that may be related to changes in renal function (e.g. routine urinalysis, elevated serum BUN and creatinine, decreased creatinine clearance, electrolyte imbalance, decrease in urine output, proteinuria, etc)

Patients should be thoroughly evaluated to rule out any alternative etiology (e.g., disease progression, infections etc.)

Steroids should be considered in the absence of clear alternative etiology even for low grade events (Grade 2) , in order to prevent potential progression to higher grade event. Guidelines for the management of patients with immune-mediated neurotoxic events are provided in Table 1.

### **10.1.4. Immune-related adverse events**

Based on the mechanism of action of durvalumab and tremelimumab leading to T-cell activation and proliferation, there is a possibility of observing irAEs during the conduct of this study. Potential irAEs may be similar to those seen with the use of ipilimumab, BMS-936558 (anti-PD-1 mAb), and BMS-936559 (anti-PD-L1 mAb) and may include immune-mediated enterocolitis, dermatitis, hepatitis (hepatotoxicity), pneumonitis, and endocrinopathies (Hodi et al 2010, Brahmer et al 2012). These AEs are inflammatory in nature and can affect any organ. With anti-PD-L1 and anti-CTLA-4 combination therapy, the occurrence of overlapping or increasing cumulative toxicities that include irAEs could potentially occur at higher frequencies than with either durvalumab or tremelimumab monotherapy. Patients should be monitored for signs and symptoms of irAEs. In the absence of an alternate etiology (eg, infection or PD), an immune-related etiology should be considered for signs or symptoms of enterocolitis, dermatitis, pneumonitis, hepatitis, and endocrinopathy. In addition to the dose

modification guidelines provided in Table 1, it is recommended that irAEs are managed according to the general treatment guidelines outlined for ipilimumab. These guidelines recommend the following:

- Patients should be evaluated to identify any alternative etiology.
- In the absence of a clear alternative etiology, all events of an inflammatory nature should be considered immune related.
- Symptomatic and topical therapy should be considered for low-grade events.
- Systemic corticosteroids should be considered for a persistent low-grade event or for a severe event.
- More potent immunosuppressives should be considered for events not responding to systemic steroids (eg, infliximab or mycophenolate).
- If the Investigator has any questions in regards to an AE being an irAE, the Investigator should immediately contact the Study Physician. Assessment of safety parameters

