Based on the mechanism of action of durvalumab or tremelimumab leading to T-cell activation and proliferation, there is the possibility of observing immune related Adverse Events (irAEs) during the conduct of this study. Potential irAEs include immune-mediated enterocolitis, dermatitis, hepatitis, and endocrinopathies. Subjects should be monitored for signs and symptoms of irAEs. In the absence of an alternate etiology (e.g., infection or PD) signs or symptoms of enterocolitis, dermatitis, hepatitis, and endocrinopathy should be considered to be immune-related.

Dose modification recommendations and toxicity management guidelines for immune-mediated reactions, for infusion-related reactions, and for non-immune-mediated reactions are detailed in Appendix 1.

In addition, management guidelines for adverse events of special interest (AESIs) are detailed in Section 10.1.3. All toxicities will be graded according to NCI CTCAE v4.03

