### 6.2.3 Toxicity management guidelines for combination treatment regimen

Combination of Durvalumab, tremelimumab and FOLFOX has never been evaluated. Any potential overlapping toxicity may occur following treatment with this combination and will be difficult to assess. Toxicity will not be managed individually but will be managed according to the guidelines described in section 6.2.1 and 6.2.2 and both treatments will be adjusted simultaneously.

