| Infliximab should not be used for management of immune-related hepatitis.                                                                       |                                                                                                                                                                                                                                                                       |                                                                                                                                                                                                                                                                                                                       | 
 
Monitor and evaluate liver function test: AST, ALT, ALP, and TB.
 
Evaluate for alternative etiologies (e.g., viral hepatitis, disease progression, concomitant medications).
 
                                                                                                                                                                                                                                                                                                                                                                                                                                                                                                                                                                                                                                                                                                                                                                                                                                                                                                 |

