|                                                                                                                                                 | Grade 2
(AST or ALT >3.0 $\times$ ULN and $\leq 5.0 \times$ ULN if baseline normal, >3-5 $\times$ baseline if baseline abnormal; and/or TB >1.5 $\times$ ULN and $\leq 3.0 \times$ ULN if baseline normal, >1.5-3.0 $\times$ baseline if baseline abnormal) | 
 
Hold study drug/study regimen dose until resolution to Grade<math>\leq 1</math>.
 
If toxicity worsens, then treat as Grade 3.
 
If toxicity improves to Grade<math>\leq 1</math>, resume study drug/study regimen after completion of steroid taper.
 
 | For Grade 2: 
 
Regular and frequent checking of LFTs (e.g., every 1 to 2 days) until elevations of these are improving or resolved.
 
If no resolution to <math>\leq</math>Grade 1 in 1 to 2 days, consider, as necessary, discussing with study physician.
 
If event is persistent (>3 to 5 days) or worsens, promptly start prednisone 1 to 2 mg/kg/day PO or IV equivalent.
 
If still no improvement within 3 to 5 days despite 1 to 2 mg/kg/day of prednisone PO or IV equivalent, consider additional work up and start prompt treatment with IV methylprednisolone 2 to 4 mg/kg/day.
 
If still no improvement within 3 to 5 days despite 2 to 4 mg/kg/day of IV methylprednisolone, promptly start immunosuppressives (i.e., mycophenolate mofetil).a Discuss with study physician if mycophenolate mofetil is not available.
 Infliximab should NOT be used.
 
Once the patient is improving, gradually taper steroids over <math>\geq 28</math> days and consider prophylactic antibiotics, antifungals,
 
 |

and anti-PJP treatment (refer to current NCCN guidelines for treatment of cancer-related infections).a

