| 
Grade 3
 (AST or ALT >5.0×ULN and ≤20×ULN if baseline normal, >5-20× baseline if baseline abnormal; and/or TB >3.0×ULN and ≤10.0×ULN if baseline normal, >3.0-10.0× baseline if baseline abnormal)
 | 
For elevations in transaminases ≤8×ULN, or elevations in TB ≤5×ULN:
 
 
• Hold study drug/study regimen dose until resolution to Grade≤1
 
• Resume study drug/study regimen if elevations downgrade to Grade≤1 within 14 days and after completion of steroid taper.
 
• Permanently discontinue study drug/study regimen if the elevations do not downgrade to Grade≤1 within 14 days.
 
 
For elevations in transaminases >8×ULN or elevations in bilirubin >5×ULN, permanently discontinue study drug/study regimen.
 | 
For Grade 3 or 4:
 
 
– Promptly initiate empiric IV methylprednisolone at 1 to 4 mg/kg/day or equivalent.
 
– If still no improvement within 3 to 5 days despite 1 to 4 mg/kg/day methylprednisolone IV or equivalent, promptly start treatment with immunosuppressive therapy (i.e., mycophenolate mofetil). Discuss with study physician if mycophenolate is not available. Infliximab should NOT be used.
 
– Request Hepatology consult, and perform abdominal workup and imaging as appropriate.
 
– Once the patient is improving, gradually taper steroids over ≥28 days and consider prophylactic antibiotics, antifungals, and anti-PJP treatment (refer to current NCCN guidelines for treatment of cancer-related infections).a
 
 |

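### Section 10.1.4 offers infliximab for steroid-refractory immune-related events, hepatitis included, without the hepatitis exception in Appendix 1, and the guideline pointers in 10.1.3 and 10.1.4 lead to the contraception table

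*Protocol*

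**What the plan says.** Section 10.1.4 of the protocol covers hepatitis. It lists it among the potential immune-related events and says that, absent another cause, "an immune-related etiology should be considered for signs or symptoms of enterocolitis, dermatitis, pneumonitis, hepatitis, and endocrinopathy". It then refers to dose guidance and adds general management advice: "modification guidelines provided in Table 1, it is recommended that irAEs are managed according to the general treatment guidelines outlined for ipilimumab". One of the bullets that follow reads "More potent immunosuppressives should be considered for events not responding to systemic steroids (eg, infliximab or mycophenolate". No organ is excepted.

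Appendix 1 treats hepatitis separately. Its general hepatitis row, not only the rows reserved for hepatocellular carcinoma, states: "Infliximab should not be used for management of immune-related hepatitis". The bar is repeated at the step where a second-line agent is introduced. At Grade 2 the instruction is "promptly start immunosuppressives (i.e., mycophenolate mofetil"; at Grade 3 or 4 it is "promptly start treatment with immunosuppressive therapy (i.e., mycophenolate mofetil".

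Section 6.2.1 routes the reader to Appendix 1: "toxicity management guidelines for immune-mediated reactions, for infusion-related reactions, and for non-immune-mediated reactions are detailed in Appendix 1". Section 6.2.3 does so by way of 6.2.1: "Toxicity will not be managed individually but will be managed according to the guidelines described in section 6.2.1 and 6.2.2". Section 6.2.1 also says that guidance on adverse events of special interest is found in section 10.1.3, where hepatitis is a listed event.

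**The concern.** Two passages of one protocol give second-line advice for the same event, and only one carries the safety restriction. An investigator who works from Section 10 on immune hepatitis that has failed steroids can choose infliximab in line with 10.1.4, and so give a drug that Appendix 1 bars for that event.

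The usual protection against such a gap is a pointer from the short text to the detailed one. Here the pointers do not work. The hepatic entry in 10.1.3 and the text of 10.1.4 both forward the reader to Table 1, and Table 1 (section 7.1) is the list of contraceptive methods. What is at stake is patient safety in a small set of events, not the trial's inference.

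**Working it through.** No arithmetic applies beyond counting. The check sets the texts side by side.

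**1. Is hepatitis within the scope of the 10.1.4 bullet?** Yes. The section names hepatitis twice, and the bullet applies to events of any kind that do not respond to steroids.

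**2. Does the Appendix 1 bar apply to this trial's patients?** Yes. It stands in the general hepatitis row and again under Grade 2 and under Grade 3 or 4: three statements outside the hepatocellular carcinoma rows.

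**3. How far do the two texts diverge?** Appendix 1 has ten organ sections that apply here, leaving out the hepatocellular carcinoma rows.

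| Appendix 1 position on infliximab | Organ sections | Count |
|---|---|---|
| Named as an option | pneumonitis, diarrhea/colitis, myocarditis, myositis | 4 |
| Barred | hepatitis | 1 |
| Not mentioned | nephritis, rash, endocrinopathy, neurotoxicity, peripheral neuromotor syndromes | 5 |
| Total | | 10 |

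The generic example in 10.1.4 therefore meets a prohibition in 1 of 10 sections. It agrees with Appendix 1 in 4.

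**4. Does Appendix 1 use the same generic wording?** Its general considerations also name a TNF inhibitor, with infliximab as the example, for steroid-refractory events. That sentence, however, tells the reader to consult the individual organ sections for the type of immunosuppressive. The 10.1.4 bullet has no such deferral.

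**5. Where do the pointers lead?**

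- *Route through Section 6.* Section 6.2.1 cites Appendix 1 three times, and 6.2.3 sends the reader to 6.2.1. This route works.
- *Route through Section 10.* In 10.1.3, eight entries refer to Table 1 for management guidance: pneumonitis, hypersensitivity, hepatic, gastrointestinal, endocrine, pancreatic, neurotoxicity and nephritis. Section 10.1.4 adds one, so 8 + 1 = 9. All nine lead to the contraception table. Appendix 1 is named 0 times in these two sections. The only other guidance that 10.1.4 invokes is the external ipilimumab guidelines, for which it gives no citation.

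**6. What does each choice of drug imply for steroid-refractory hepatitis?**

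- Mycophenolate: consistent with 10.1.4 and with Appendix 1.
- Infliximab: consistent with 10.1.4, barred by Appendix 1.

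No sentence says which text prevails. The protocol gives no frequency of steroid-refractory hepatitis, so the number of patients exposed to the gap cannot be estimated from it.

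**The case against.** The strongest reply is that nothing here is contradictory. The bullet is general and permissive, it advises infliximab for no particular organ, and one of its two examples is the agent that Appendix 1 requires. A general statement and a specific rule that qualifies it can be read together. This stands. A reader might infer that 10.1.4 expressly contradicts Appendix 1, or that it instructs the use of infliximab in hepatitis; the text supports neither reading.

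A reader might also infer that the protocol gives no working route to the restriction, or that Table 1 is the only guidance 10.1.4 mentions. Neither is so. Section 6.2.1 names Appendix 1 directly, and the wording in 6.2.3 is directive where 10.1.4 only recommends. Section 10.1.4 also cites the ipilimumab guidelines, though these lie outside the protocol.

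The failure path is narrow as well. Section 10.1.4 gives no steroid dose, grade thresholds or rules on holding treatment. An investigator who manages hepatitis by the protocol will need the Appendix 1 rows before reaching second-line therapy, and the bar is written into that very step. Appendix 1 calls for a hepatology consult at Grade 3 or 4. Section 10.2.3.2 requires reporting within 24 hours, and sponsor evaluation, when transaminases above 3 times the upper limit of normal coincide with bilirubin above 2 times that limit, unless an unrelated diagnosis is confirmed; that covers only part of the hepatic events. Finally, a reader sent to a contraception table will see at once that the reference is wrong.

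These points make the concern smaller without removing it. Section 10.1.4 is operative safety guidance and not background, it lacks the deferral that Appendix 1's own general text carries, and 6.2.1 itself sends readers to the section whose pointers fail.

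**Conclusion.** The point holds as an omitted exception combined with wrong cross-references. Section 10.1.4 offers infliximab for steroid-refractory events that include hepatitis, without the restriction that Appendix 1 states three times, and nine of nine toxicity-guideline pointers within the protocol in 10.1.3 and 10.1.4 lead to the contraception table.

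Its size is small: one organ section of ten, a choice in which the other named drug is correct, and a working route to Appendix 1 elsewhere. It does harm only if an investigator reaches second-line treatment of immune hepatitis from Section 10 without opening Appendix 1. It should be corrected as a minor matter of patient safety. No endpoint, sample size or error rate depends on it.

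The conclusion rests on the protocol text alone. It assumes that Appendix 1 is meant to govern, which its detail and the routing in 6.2.1 suggest but no sentence states.

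**What to change.** Make three wording changes in one amendment.

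1. In the 10.1.4 bullet on more potent immunosuppressives, add: *except immune-related hepatitis, where infliximab must not be used (mycophenolate mofetil per Appendix 1)*.
2. Change the nine references to Table 1 (eight entries in 10.1.3 and one in 10.1.4) to Appendix 1.
3. Add one sentence stating that Appendix 1 governs toxicity management wherever another section differs from it.

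The cost is editorial. No visit, sample, patient or analysis changes.
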